### **4.3 Recruitment, identification and consent of potential participants**

Potential participants will be identified as they change oxygen therapy from standard nasal cannula or mask to high flow nasal cannula or NIV. When a FiO2 of 0.5 is required to reach a SpO2 of 94% the patients will be approached.

Patients will receive oral, followed by written information and provided an appropriate time for consideration and if needed, consultation with the treating physician, a family member, and/or another person of their choice. Written informed consent will be obtained prior to recruitment into the trial. Due to restrictions in transfer of e.g. paper from single patient rooms, the informed consent procedure may include a proxy in the room transferring the information to and from the patient, or a digital transfer (photo of the informed consent form)

### **4.4 Subject withdrawal**

Any refusal or withdrawals from the study will be documented, with the reason recorded. The investigator or treating physician may withdraw a patient from the study at any time if it is deemed it is no longer safe to continue with the allocated treatment.

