### 5.4 Protocol termination

Every participant follows the allocated intervention until protocol termination criteria are met. Termination criteria are fulfilled if:

- the patient recovers and standard nasal prongs or open face mask ("oxymask") with a maximal flow of 5 L/min can be used to manage the hypoxemia for at least 12 hours.
- the patient is intubated.

- death occurs.

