## 6. RANDOMIZATION AND BLINDING

Patients will be randomized 1:1 in blocks of four at each center. The randomization outcome is obtained via a web-based service provided by the coordinating center. The patient, the treating physician/-s and other care providers will not be blinded to the study allocation. Assessors will be blinded during analysis.

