## 7. OUTCOMES

### 7.1 Primary Outcome

The primary outcome is the rate of intubation.

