## 8.3 Statistical analysis

Intention-to-treat analyses will be conducted based on available data. The difference in rate of intubation between the groups will be analyzed with the Chi-2 test. Continuous data will be compared using multifactorial repeated measures ANOVA or multiple regression. Mean values with 95% confidence intervals will be calculated for primary and secondary outcomes. Non-parametric tests will be used for non-normally distributed data, with descriptive data expressed as medians with interquartile range.

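### Section 4.4 lets a safety stop of the allocated treatment end study participation, and nothing in the protocol secures the intubation outcome afterwards

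*Protocol*

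**What the plan says.** Section 4.4 contains two rules. The first is administrative: "Any refusal or withdrawals from the study will be documented, with the reason recorded". The second gives clinicians discretion: "The investigator or treating physician may withdraw a patient from the study at any time if it is deemed it is no longer safe", and the sentence completes the condition as "no longer safe to continue with the allocated treatment". The patient leaves the study, while the reason concerns the treatment.

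Section 5.4 (Protocol termination) states that "Every participant follows the allocated intervention until protocol termination criteria are met". It lists three such criteria: recovery to low-flow oxygen, intubation and death.

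On the analysis, section 7.1 states "The primary outcome is the rate of intubation". Section 8.3 states "Intention-to-treat analyses will be conducted based on available data" and "The difference in rate of intubation between the groups will be analyzed with the Chi-2 test". Section 8.1 allows for 10% drop-out.

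Section 6 makes the trial open label at the bedside: "The patient, the treating physician/-s and other care providers will not be blinded to the study allocation". Section 5.1.2 sets a target of 16 hours in 24 for the prone arm. In the standard care arm it leaves prone positioning to the treating physician.

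**The concern.** A randomised comparison is protected when stopping the assigned treatment and stopping follow-up are separate events. Section 4.4 merges them. A site that follows it literally may stop recording outcomes once the allocated treatment is judged unsafe, because the patient has left the study. Section 8.3 then analyses what is available.

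Three features make such a loss potentially informative:

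- The decision lies with clinicians who know the allocation.
- A safety judgement in hypoxaemic respiratory failure may be related to the risk of intubation, which is the primary outcome.
- Standard care has no protocolised positioning, so there is less allocated treatment that could be judged unsafe.

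If patients close to intubation left the prone arm more often than the control arm, the observed prone-arm rate would fall without any treatment effect.

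**Working it through.** **The plan's own figure.** Section 8.1 gives 112 per group for 88% in control and a 20% decrease, power 90%, alpha 0.05. Read as a relative decrease, the prone rate is 0.88 × 0.80 = 0.704. With the two-sided pooled formula, n = [1.960 × √(2 × 0.792 × 0.208) + 1.2816 × √(0.88 × 0.12 + 0.704 × 0.296)]² / 0.176² = 110 per group, within 2 of the stated 112. The sample size is not in dispute here. The figure fixes 88% as the only intubation rate that the protocol states.

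**Inputs for the illustration.**

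- From the protocol: 240 patients randomised 1:1, so 120 per arm; true rate p = 88%; two-group test of proportions at 0.05, taken as two-sided.
- Assumed: no true effect; w = 12 prone patients (10% of 120) lost, each of whom would have been intubated, with none of these intubations counted; no loss in control. The protocol's 10% is a trial-wide allowance for drop-out from any cause, so placing it all in one arm and all before intubation is an extreme.
- Also assumed, to show sensitivity: p = 50%. This rate is not in the protocol.

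**Observed prone rate** = (120p − w) / (120 − w).

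- p = 88%: (105.6 − 12) / 108 = 86.7%. Bias −1.3 points, a spurious relative reduction of 1.3/88 = 1.5%.
- p = 50%: (60 − 12) / 108 = 44.4%. Bias −5.6 points, a spurious relative reduction of 5.6/50 = 11%.

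**Error rate.** Let d be the bias, SE₀ the pooled standard error and SE₁ the unpooled one. The chance of a false benefit is 1 − Φ((1.96 SE₀ − d)/SE₁) and of a false harm Φ((−1.96 SE₀ − d)/SE₁).

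- p = 88%: SE₀ = 0.0441, SE₁ = 0.0442, d = 0.0133. False benefit 4.9%, false harm 1.2%, total 6.1%.
- p = 50%: SE₀ = 0.0662, SE₁ = 0.0661, d = 0.0556. False benefit 13.1%, false harm 0.2%, total 13.3%.

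**Softer assumptions.**

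| Lost before intubation (prone / control) | Bias at 88% | Two-sided error | Bias at 50% | Two-sided error |
|---|---|---|---|---|
| 12 / 0 | 1.3 points | 6.1% | 5.6 points | 13.3% |
| 6 / 0 | 0.6 points | 5.3% | 2.6 points | 6.9% |
| 8 / 4 | 0.4 points | 5.1% | 1.8 points | 5.9% |

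If the withdrawn patients are followed and counted, the bias is zero and the error returns to 5% in every row.

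**The case against.** The strongest reply is that the risk is only possible, and small at the planned rate. At 88% even the extreme case gives a 1.5% relative reduction against a planned 20%. That stands, and it limits the severity. The larger figures need a lower true rate, which is an assumption.

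A reader might go further than the text in four ways, and the documents do not support these readings.

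- *That withdrawn patients are certainly excluded.* Section 8.3 refers to available data. It does not say that data obtained after withdrawal are discarded, and no section forbids collecting them.
- *That the trigger is deterioration.* Section 4.4 speaks only of safety. Section 9 names pressure wounds, aspiration and cardiac arrest as possible adverse events, and a pressure wound need not precede intubation. A patient who deteriorates can be intubated at the intensivist's discretion (section 5.3), which counts as the primary outcome.
- *That the loss is one-sided.* Section 4.4 covers both arms, and standard-care patients may be proned. The imbalance is a reasonable inference from the design, not a stated fact.
- *That sections 4.4 and 5.4 contradict each other.* One governs participation and the other the duration of the intervention, so they can coexist. What is missing is a stated way to stop the intervention for safety and remain in follow-up.

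It can also be said that missing data belong in a statistical analysis plan. That holds for methods such as sensitivity analyses, and their absence is not criticised here. It does not settle this point, because an analysis plan cannot recover outcomes that sites stopped recording. Whether follow-up continues after treatment stops is a rule of conduct, and the protocol sets it.

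**Conclusion.** The point holds as a weakness in a conduct rule. Section 4.4 turns a safety judgement about treatment into an exit from the study, section 8.3 relies on available data, and nothing keeps intubation status in between. Such losses could favour the prone arm. Their number and balance between arms are unknown.

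With the extreme assumption of 12 prone losses, all just before intubation and none in control, the bias is about 1.3 points at the protocol's 88% and about 5.6 points at an assumed 50%. Fewer or more balanced losses shrink it quickly. These figures illustrate how the bias depends on the assumptions and do not predict what will happen. The point should be fixed because the remedy is simple, but the documents do not show that the primary result would be seriously distorted.

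**What to change.** - **Section 4.4:** state that the investigator or treating physician may discontinue the allocated treatment; that the patient then stays in the study, with intubation, mortality and the other planned outcomes still collected; and that only withdrawal of consent ends data collection.
- **Section 8.3:** state that all randomised patients are analysed in the arm to which they were allocated, including those who stopped the allocated treatment.

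The clinician's freedom to stop prone positioning is untouched. The cost is a short wording change in two sections, plus continued recording, for the patients concerned, of outcomes that sections 7.1 and 7.2 already plan. The design, sample size and primary test do not change.

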## 5. INTERVENTIONS

### 5.1 Treatment arms

There are two arms, the prone positioning arm and the standard care arm.

#### 5.1.2 Standard care arm

PP is neither prohibited nor encouraged and may be prescribed by the treating physician at their discretion.

#### 5.1.2 Prone positioning arm

The patient, the treating physician/-s and other providers of care are informed of the study allocation and a protocol for PP is initiated with a target PP of 16/24 hours. Prone positioning is defined as:

1. Prone position. Pillows may be used. Patient may position their arms at their choice. Bed may be at zero degrees or in a reverse Trendelenburg position as comfortable.
2. Left or right face forward position. This is to increase comfort and compliance to the protocol.

PP should be performed in coherent periods of at least two hours at a time but may be individualized (i.e. longer or shorter) as required to maximise compliance and/or to reach the target time. To be able to reach the target of 16/24 hours, PP should ideally be performed during sleep. When not in PP but in bed, patients should lay in the semi-recumbent position with the head of the bed elevated to 30 degrees or the left or right recumbent position. Flat supine positioning is discouraged. The time spent in other positions than PP should be planned for meals etc. In the ICU, sedation is allowed as indicated but is not protocolized.

### 5.3 Other aspect of care for both arms

All other interventions will follow local guidelines at the present hospital and are not affected by the study protocol. A change of oxygen therapy from HFNC to NIV or vice versa is allowed in both groups at the treating physicians discretion, however the protocol for PP is continued. If patients are transported in-hospital, oxygenation by face mask is allowed and the patient can be transported in a position appropriate for adequate monitoring and safety. The decision to intubate is made at the discretion of the treating intensivist. Patient positioning after intubation is not protocolized.

### 5.4 Protocol termination

Every participant follows the allocated intervention until protocol termination criteria are met. Termination criteria are fulfilled if:

- the patient recovers and standard nasal prongs or open face mask ("oxymask") with a maximal flow of 5 L/min can be used to manage the hypoxemia for at least 12 hours.
- the patient is intubated.

- death occurs.

## 5.5 Electrical impedance tomography - subgroup study

EIT is a non-invasive radiation-free imaging technique that provides real-time images and data of regional lung ventilation and lung volumes. Changes in EELI and TIV correlates with EELV and tidal volume respectively.

### 5.5.2 Participants, identification and recruitment

60 patients (15 patients allocated to PP and 15 patients allocated to standard care in the groups of patients treated with HFNC and NIV respectively) that are admitted to the ICU and previously included in the present trial. Participants will have signed a written informed consent for this part of the study at inclusion but may withdraw from this subgroup study when approached at the ICU or at any other time.

*Amendment February 2021: if inclusion of patients for the main study is terminated prematurely after an interim analysis due to futility or efficacy, we plan to continue inclusion of patients only for the physiologic study the effects of prone position on lung aeration according to 5.5.1.*

### 5.5.1 EIT protocol and measurements.

An elastic EIT-band will be placed around the lower thoracic wall and connected to an EIT-device. Participants will be put in a semi-recumbent position in the bed, with the head elevated to 30 degrees and receive HFNC at a rate of 50 L/min or NIV with the current individual settings, including the FiO2 required to reach an SpO2 of 92-96%. After stable SpO2-values are confirmed, base-line recordings of arterial blood gas results, RR, EIT-measurements and hemodynamic parameters are collected. Participants will thereafter be placed in the prone position with the bed at 0 degrees angle. Pillows are allowed for comfort. The measurements will be repeated at 30 and 60 minutes after start of PP. This is followed by a second semi-recumbent positioning as above with repeated measurements after 30 minutes. Flow rate and FiO2 will remain unchanged during the study period unless desaturation < 90% for more than 5 min, or < 85% for more than 1 min occurs. Dyspnea assessed with the modified Borg-scale will be recorded at baseline, after 30 and 60 min in PP and after 30 min in second semirecumbent positioning.

## 6. RANDOMIZATION AND BLINDING

Patients will be randomized 1:1 in blocks of four at each center. The randomization outcome is obtained via a web-based service provided by the coordinating center. The patient, the treating physician/-s and other care providers will not be blinded to the study allocation. Assessors will be blinded during analysis.

### 6.1 Concealment mechanism

An on-line central randomization service will be used.

## 7. OUTCOMES

### 7.1 Primary Outcome

The primary outcome is the rate of intubation.

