## PROTOCOL SYNOPSIS

**English title:** Awake prone positioning with high flow nasal oxygen in critically ill covid-19 patients.

**Swedish title:** Buklägesbehandling med högflödesgrimma vid covid-19.

**Objectives:** Determine if a protocol for prone positioning with high flow nasal cannula or noninvasive ventilation reduces the rate of intubation in awake spontaneous breathing covid-19 patients or patients with other infectious disease with moderate to severe hypoxemic respiratory failure.

**Design:** Multicenter randomized controlled, parallel group, superiority trial.

**Population and Intervention:** 240 adults, 18 years or older with confirmed or strongly suspected infection with novel corona virus SARS-CoV-2 or other infectious disease, ongoing or planned oxygen treatment with high flow nasal cannula or noninvasive ventilation and moderate to severe respiratory failure as defined by a  $\text{PaO}_2/\text{FiO}_2$  ratio of  $\leq 20$  kPa ( $\approx 150$  mmHg) and/or a  $\text{FiO}_2$  of 0.5 required to reach an  $\text{SpO}_2$  of 94%.

Patients will be randomized 1:1 to a prone positioning protocol with a prone position target of 16 hours/day OR standard care.

**Outcomes:** Primary outcome is the rate of intubation. Secondary outcomes include time in prone position, admission to the ICU, time on mechanical ventilation, need for renal replacement therapy, the WHO ordinal scale for clinical improvement and the 7- and 30-day mortality and complication rate.

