## **2.1 Aim(s)**

The primary aim of this study is to determine the effect on prone positioning with HFNC or NIV on the intubation rate in critically ill COVID-19 patients or patients with other infectious disease with moderate to severe hypoxemic respiratory failure. The secondary aims include time/day in PP, 7- and 30-day mortality, days on ventilator, in-hospital and ICU LOS, incidence of RRT, the need for vasopressors and/or inotropic drugs, the WHO ordinal scale for clinical improvement, and adverse events during PP. In a subset of 30 patients we aim to study the acute effects on lung volume and function with EIT, PaO2/FiO2 ratios, respiratory rate, hemodynamic parameters and effect on dyspnea.

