### 7.2 Secondary outcomes

- time in PP/day in awake PP if measured. This will vary at different sites and wards.
- cross-over rate to NIV,
- incidence and days of vasopressor and/or inotropic support,
- incidence and days of renal replacement therapy,
- days on ventilator for patients in need of mechanical support,
- number of patients receiving extracorporeal membrane oxygenation,
- in-hospital and ICU LOS,
- complications.
- the 7- and 30-day mortality.
- WHO ordinal scale (Fig 1) for clinical improvement at baseline, day 7 and 30.

*Fig 1. WHO ordinal scale for clinical improvement*

| Patient State  | Description                                      | Score |
|----------------|--------------------------------------------------|-------|
| Uninfected     | No clinical or virological evidence of infection | 0     |
| Ambulatory     | No limitations of activities                     | 1     |
|                | Limitations of activities                        | 2     |
| Hospitalized   |                                                  |       |
| Mild disease   | No oxygen therapy                                | 3     |
|                | Oxygen by prongs or mask                         | 4     |
| Severe disease | NIV or HFNC                                      | 5     |
|                | Intubation and mechanical ventilation            | 6     |

|      |                                                                              |   |
|------|------------------------------------------------------------------------------|---|
|      | Mechanical ventilation
+additional organ support
(pressors, RRT, ECMO) | 7 |
| Dead | Death                                                                        | 8 |

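### The primary outcome, intubation, has no time window, and by default a death without intubation counts the same as recovery

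*Protocol*

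**What the plan says.** Every place in the protocol that names the primary outcome leaves it open in time:

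- Synopsis: "Primary outcome is the rate of intubation".
- Section 2.1: "The primary aim of this study is to determine the effect on prone positioning with HFNC or NIV on the intubation rate".
- Section 7.1, the whole definition: "The primary outcome is the rate of intubation".
- Section 8.1 assumes an 88% control intubation rate, also without a period.
- Section 8.3: "The difference in rate of intubation between the groups will be analyzed with the Chi-2 test", preceded by "Intention-to-treat analyses will be conducted based on available data".

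Time points do appear for two secondary outcomes in section 7.2: "the 7- and 30-day mortality", and the WHO ordinal scale "for clinical improvement at baseline, day 7 and 30".

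Section 5.4 says "Every participant follows the allocated intervention until protocol termination criteria are met" and lists recovery, intubation and death as three separate criteria. Section 4.2.2 excludes patients who already have a decision against intubation. Under section 5.3 the treating intensivist decides whether to intubate, and under section 6 care providers know the allocation.

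**The concern.** Two things are left open in the single confirmatory comparison.

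The first is the period over which intubation counts. A patient who recovers enough to leave the allocated intervention and is intubated later could be classed either way. The interim looks in section 8.2 are triggered by inclusion of 120 and 180 patients, not by completed follow-up, so recently enrolled patients could enter them as not intubated.

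The second is the status of death before intubation. Without a rule, such a death falls in the same cell of the 2×2 table as recovery. Intubation is a discretionary decision by clinicians who know the allocation. If intubation were delayed more in one arm and some of those patients died unintubated, that arm would look better on the primary outcome. The efficacy stopping criterion in section 8.2 rests on the same rate.

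**Working it through.** **1. The plan's own figure.** Inputs from section 8.1: control rate p₁ = 0.88; 20% decrease, read as relative, so p₂ = 0.88 × 0.80 = 0.704; power 90%; alpha 0.05, taken as two-sided. Pooled formula without continuity correction, with p̄ = (p₁ + p₂)/2 = 0.792:

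n = [1.96·√(2p̄(1−p̄)) + 1.2816·√(p₁(1−p₁) + p₂(1−p₂))]² / (p₁−p₂)² → 110 per arm.

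The stated 112 is within 2 patients of this, and power at 112 per arm is 90.6%. The figure uses neither a follow-up time nor a rule for deaths, so it neither supports nor weakens the point.

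**2. Is a window given indirectly?** Days 7 and 30 are attached to mortality and the WHO scale only. Section 5.4 sets when the allocated intervention ends, by events that differ between patients. It does not say how long intubation is ascertained. No window can be derived from either.

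**3. Where does an unintubated death go?** Section 5.4 lists death apart from intubation, so such deaths are foreseen. The entry exclusion in section 4.2.2 does not reach treatment limits set after enrolment or sudden death; section 9 itself lists cardiac arrest as a possible adverse event. In an intention-to-treat proportion the patient is in the denominator and not in the numerator. No composite, competing-risk or other rule changes that.

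**4. How far could the test be moved?** Assume that intubation-or-death is truly 88% in both arms, that no control patient dies unintubated, and that a share x of the prone arm does. Intubation rates are then 0.88 and 0.88 − x. With 112 per arm, the chance of significance in favour of prone positioning is

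Φ[(x − 1.96·SE₀)/SE₁], where SE₀ = √(2p̄(1−p̄)/112) and SE₁ = √((p₁(1−p₁) + p₂(1−p₂))/112).

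| Assumed excess x | Rates compared | SE₀ | SE₁ | Chance of significant apparent benefit |
|---|---|---|---|---|
| 0 points | 88% v 88% | 0.0434 | 0.0434 | 2.5% |
| 2 points | 88% v 86% | 0.0449 | 0.0449 | 6.5% |
| 3 points | 88% v 85% | 0.0457 | 0.0456 | 9.6% |
| 5 points | 88% v 83% | 0.0471 | 0.0469 | 18.4% |

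Worked for 5 points: (0.05 − 1.96 × 0.0471)/0.0469 = −0.90, and Φ(−0.90) = 0.184. Exact binomial enumeration of the uncorrected chi-square test gives 9.9% at 3 points and 18.8% at 5 points, so the approximation is adequate. An excess in the control arm would move the test the other way.

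**5. What would a composite primary outcome do to power?** Start from 88% v 70.4% intubation and add assumed unintubated deaths, at 112 per arm:

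| Assumed unintubated deaths | Composite rates | Power | n per arm for 90% power |
|---|---|---|---|
| 2% in prone arm only | 88% v 72.4% | 83.9% | 136 |
| 5% in prone arm only | 88% v 75.4% | 68.6% | 196 |
| 2% in both arms | 90% v 72.4% | 92.6% | 102 |
| 5% in both arms | 93% v 75.4% | 95.6% | 89 |

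Power can move in either direction.

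**The case against.** The strongest reply has four parts.

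- **The scoring of deaths is inferred.** A reader might conclude that the protocol declares an unintubated death a success. It does not. It is silent, and a statistical analysis plan that is not shown could settle the handling. This stands as a limit on the wording. It does not remove the point, because the time frame of the primary outcome and the status of death define the outcome, and that belongs in the protocol.
- **The bias needs an imbalance that nobody has documented.** With unintubated deaths equal in both arms, the lean disappears in the setting of step 4. The entry criteria also make such deaths less likely, by excluding known treatment limits, terminal illness and severe haemodynamic instability. This stands: the size of the effect is unknown.
- **Harm would be visible.** Mortality at 7 and 30 days and the WHO scale, with death as its worst score, are secondary outcomes. Deaths possibly related to prone positioning are serious adverse events under section 9. True, but none of this changes the primary test or the efficacy criterion in section 8.2.
- **Intubation alone is a legitimate question.** Sections 2 and 2.2 motivate it by ventilator shortage, and fewer intubations would then be a true result on the stated outcome. This also stands. It argues for keeping intubation as primary and reading it beside deaths, not for leaving deaths without a rule.

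**Conclusion.** The point holds. The absence of a time window is certain from the text. That an unintubated death counts as not intubated is the default consequence of an intention-to-treat proportion with no rule to the contrary.

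The size is conditional: about 2.5%, 6.5%, 10% or 18% for an excess of 0, 2, 3 or 5 points in the prone arm, assuming intubation-or-death equal at 88%, 112 per arm and no unintubated deaths among controls. A reader might infer that the trial's false-positive risk is 18%. The documents do not support that: they give no rate of unintubated death and no reason to expect it to differ by arm.

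A reader might also infer that the primary outcome must become a composite at no more cost than a change of wording. That does not follow, because the 88% and the 112 per group in section 8.1 were set for intubation alone.

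**What to change.** Rewrite section 7.1, and align the synopsis and sections 2.1 and 8.3, so that the primary outcome reads: *intubation within 30 days of randomisation*. This matches the later time point already used for mortality and the WHO scale.

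Pre-specify *intubation or death within 30 days* as the key supportive analysis. Report intubation and death without intubation separately by arm, and state that a reduction in intubation will be interpreted alongside that analysis.

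The cost is one extra analysis and ascertainment of intubation to day 30. Thirty-day mortality is already collected, and the sample size is unchanged.

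Making the composite the primary outcome remains an option for the sponsor. In that case section 8.1 must be rechecked with an explicit assumption about unintubated deaths in each arm.
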